### Statistical analysis

Patients’ baseline characteristics will be summarized based on groups. Continuous variables will be described using the mean (standard deviation), or the median (interquartile range) if the normality assumption is violated. Student’s *t* test or Wilcoxon rank sum test (if normality is violated) will be used for comparison of continuous variables among the two groups. Categorical variables will be described using the frequency (percentage) and compared using the chi-squared test.

For the primary comparison, the chi-squared test will be used for the response rate (the proportion of participants whose pain reduced ≥ 50% compared with baseline). For the secondary outcomes, Student’s *t* test, chi-squared test, Fisher’s exact test or the Wilcoxon rank sum test will be used to test the difference of the outcomes including the total pain, remedial analgesia, re-visit and admission rate, blinding assessment, credibility and expectancy, and adverse events, between groups according to the distribution of variables. There is no interim analysis or additional analysis in this trial.

All efficacy analyses will be performed using the intention-to-treat set, which includes all randomized patients. Missing data will be dealt with the last observation carried forward (LOCF). All analyses will be performed using SPSS version 23.0 (IBM SPSS Statistics, NY, USA). The level of significance will be established at *α* < 0.05 with a two-sided test.

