### Inclusion criteria

Diagnosed as ARCUC according to the guideline of the European Association of Urology (2017) [1]Aged 18–75 years (either sex)Pain intensity of 4 or more out of 10 on a visual analog scale (VAS) [14]Written informed consent

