### Outcomes

#### Primary outcome

The primary outcome will be the response rate after 10 min of puncturing of the needles, which is defined as the proportion of participants whose pain score on VAS reduces at least 50% compared with baseline [5].

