#### Secondary outcomes

##### Total pain

The total pain will be defined by the area under the curve during the 60 min after puncturing the needles [17]. The pain will be assessed using a VAS [14] with scores ranging from 0 to 10 after 0, 1, 5, 10, 15, 20, 30, 45, and 60 min of puncturing of the needles. The bigger area under the curve indicates worse pain.

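### Total pain, a secondary outcome, is tested as a raw 60-minute VAS area with no baseline term; the test is valid but gives up precision that the recorded baseline VAS could supply

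*Protocol article*

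**What the plan says.** Under Secondary outcomes, the Total pain paragraph states: "The total pain will be defined by the area under the curve during the 60 min after puncturing the needles". VAS is read "after 0, 1, 5, 10, 15, 20, 30, 45, and 60 min of puncturing of the needles", on a 0 to 10 scale. Nothing is subtracted from the area or divided into it, so it is a raw area.

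The Statistical analysis section lists Student's t test among the options for secondary outcomes, and says that "the Wilcoxon rank sum test will be used to test the difference of the outcomes including the total pain", the choice depending on the distribution. No covariate is named for any test. The same section adds: "There is no interim analysis or additional analysis in this trial".

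Baseline VAS is recorded for every patient. Entry requires "Pain intensity of 4 or more out of 10 on a visual analog scale (VAS"), and the Primary outcome paragraph defines response as the "proportion of participants whose pain score on VAS reduces at least 50% compared with baseline".

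**The concern.** Two patients who enter at VAS 4 and VAS 10 can be expected to accumulate different areas over the next hour, whichever arm they are in. A two-sample test on the raw area treats that spread as noise. If baseline pain predicts later pain, two things follow:

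- The confidence interval for the treatment difference is wider than the collected data require.
- With 40 per arm, a chance difference in baseline passes into the estimated difference in area, in proportion to how strongly baseline predicts later pain.

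This cannot simply be left to an analysis plan. The protocol itself names the unadjusted tests and excludes additional analysis, so a baseline adjustment made after the data are seen would be post hoc.

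**Working it through.** **The plan's own figure.** The only sample size is for the primary response rate: 70% against 40%, two-sided 5%, at least 80% power, 40 per arm. The standard unpooled formula reproduces it: (1.960 + 0.842)² × (0.70×0.30 + 0.40×0.60) / 0.30² = 7.85 × 0.45 / 0.09 = 39.2, so 40 per arm. This point does not affect that figure. The plan gives no SD, correlation or power for total pain.

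**Inputs.** From the Protocol article: 40 per arm, two-sided 5%, the reading times, and entry VAS of 4 or more. Assumed: correlation rho between baseline VAS and the 60-minute area of 0.3, 0.5 or 0.6. For the shift calculation only: baseline SD of 1.5 points, and the same SD for the mean VAS over 60 minutes (area / 60).

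**Step 1, precision.** ANCOVA multiplies the residual variance by 1 − rho². The effect detectable with 80% power, in SDs of the area, is (1.960 + 0.842) × √(2/40) = 0.626 unadjusted and 0.626 × √(1 − rho²) adjusted. The total sample that an unadjusted test would need for the same precision is 80 / (1 − rho²).

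| rho (assumed) | Residual variance cut | Detectable effect | Power at 0.626 SD | Equivalent unadjusted total |
|---|---|---|---|---|
| none (unadjusted) | 0% | 0.626 SD | 80% | 80 |
| 0.3 | 9% | 0.598 SD | 83.6% | 88 |
| 0.5 | 25% | 0.543 SD | 89.9% | 107 |
| 0.6 | 36% | 0.501 SD | 93.8% | 125 |

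**Step 2, chance imbalance.** The standard error of the baseline difference is √(2/40) = 0.224 SD, which is 1.5 × 0.224 = 0.34 points under the assumed SD. With equal SDs, the slope of mean 60-minute VAS on baseline equals rho. A one-standard-error imbalance therefore moves the difference in area by 0.335 × 60 × rho = 20.1 × rho VAS-minutes: about 6 at rho 0.3, 10 at 0.5 and 12 at 0.6.

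**Step 3, effect on the test.** Averaged over randomisations, the type I error stays at 5%. Given a particular imbalance of k standard errors, the unadjusted statistic has mean rho × k and variance 1 − rho² under the null.

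- At k = 1, the conditional type I error is 5.0%, 4.8% and 4.5% for rho 0.3, 0.5 and 0.6, so it is not inflated.
- At k = 1.96 (0.44 SD, the edge of the 95% range), it is 7.9%, 12.9% and 16.4%.

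**Step 4, does the 0-minute reading already adjust?** No. In the trapezoid area its weight is (1 − 0)/2/60 = 0.8%. Baseline acts on the area almost wholly through its correlation with later readings.

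**The case against.** The strongest reply is that nothing here is an error. Unadjusted t and rank-sum tests are legitimate in a 1:1 randomised trial, and overall type I error is held. Total pain is secondary. The gain rests entirely on a correlation that the documents do not give. Restricting entry to VAS 4 or more narrows the baseline range, and rescue analgesia given above 8 points after needling falls on the patients with most pain. Either could weaken or bend the relation between baseline and area. At rho 0.3 the detectable effect moves only from 0.626 to 0.598 SD. All of this stands, and it keeps the point modest. It does not remove it, because the covariate is already collected and the protocol closes off its use.

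A reader might infer several stronger things that the documents do not support:

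- **That the primary analysis has the same weakness.** It is true that "For the primary comparison, the chi-squared test will be used for the response rate" with no covariate. But baseline is the denominator of each patient's response, so imbalance matters only if percentage reduction itself depends on baseline. In a simulation at 70% against 40% with 40 per arm (4,000 runs per setting), power for baseline-adjusted logistic regression against chi-squared was 79% v 80%, 81% v 81%, 81% v 80% and 86% v 80%, for correlations between percentage reduction and baseline of 0, 0.2, 0.3 and 0.5. The gain is about nil unless the dependence is strong.
- **That a one-standard-error imbalance moves the area by 20 VAS-minutes.** That needs a slope of 1, with the baseline gap persisting in full for an hour, and it conflicts with a correlation of 0.3 to 0.6 under equal SDs.
- **That randomisation should have been stratified by severity.** Its absence from the description of a single-centre trial of 80 is not a defect.

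**Conclusion.** The point holds for total pain only, as a matter of efficiency and of bias conditional on a chance imbalance, not of validity. Under assumed correlations of 0.3 to 0.6, the planned test forgoes a 9% to 36% reduction in residual variance. With an assumed SD of 1.5 points for both baseline and mean 60-minute VAS, a typical chance imbalance moves the area difference by about 6 to 12 VAS-minutes. Confidence is high that the plan fixes an unadjusted comparison. The size of the loss is uncertain because it depends on figures that the documents do not supply. The primary analysis and the sample size of 80 are not called into question.

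**What to change.** In the Statistical analysis section, replace the test for total pain with ANCOVA of the 60-minute area on arm and baseline VAS, and report the adjusted mean difference with its 95% CI. Say that the covariate is the same baseline value used to score response. Because the plan now turns to a rank-sum test when normality fails, name the replacement as well: a rank-based ANCOVA or a bootstrap CI if residuals are clearly non-normal. Amend the sentence excluding additional analysis so that it agrees.

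Leave the chi-squared test as the primary analysis. A logistic model with baseline VAS is at most an optional sensitivity analysis.

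The cost is wording, settled before unblinding. No new data or patients are needed, and the planned software fits the model.

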**Discussion:**

The finding of this trial will provide evidence on the efficacy and safety of acupuncture for the treatment of ARCUC. The results of this study will be published in peer-reviewed journals.

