## Background

Acute renal colic caused by urinary calculi (ARCUC) is described as acute unbearable paroxysmal pain in the lower back or upper abdomen, with or without hematuria, nausea, and vomiting [1]. The urinary stone disease was increasingly prevalent, with a lifetime risk of about 12% in men and 6% in women [2]. The prevalence of kidney stones in China was 6.4% (6.5% in men and 5.1% in women) [3]. In the USA, more than one million patients visit the emergency department for the ARCUC every year [4]. It is described as one of the worst pains a patient could have and has a considerable impact on quality of life.

Pain relief is the primary goal in the management of patients with ARCUC [1]. NSAIDs offer effective sustained analgesia for ARCUC in the emergency department [5] and result in a lower need for rescue analgesia [6]. The 2017 update of the European Association of Urology (EAU) guidelines recommends NSAIDs as the first-line analgesic [1]. However, its clinical application is partly limited to the increased risk of major coronary events which increase with dose and duration [7, 8]. Furthermore, the onset time of NSAIDs is relatively slow, with the time to peak plasma concentration of 10–30 min after intramuscular injection [9]. More than 30% of patients did not achieve satisfactory relief of pain after had NSAIDs [5]. Adjunctive therapy with a quick analgesia effect and less adverse events is needed for patients with ARCUC.

Acupuncture is a complementary therapy from traditional Chinese medicine, which has the advantages of quick analgesia [10, 11]. A meta-analysis suggested that acupuncture may be a potential therapy for ARCUC [12]. However, to our knowledge, there is no randomized controlled trial (RCT) to measure the efficacy of acupuncture as an adjunctive treatment to NSAIDs for ARCUC. This randomized, participant-blind, sham-controlled trial is designed to evaluate the efficacy and safety of acupuncture as an adjunctive treatment to diclofenac for ARCUC.

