#### Sample size

In this study, the sample size was priori calculated. Based on the previous literature [19] and our clinical experience, the response rates in the acupuncture group and sham acupuncture group are expected to be 70% and 40%, respectively. The ratio between acupuncture group and sham acupuncture group was 1:1. A sample size of 80 patients (40 in each group) is estimated to have at least 80% power to detect difference between groups at a 2-sided significance level of 5% according to the formula: $$ n={\left[\frac{{\mathrm{z}}_{\alpha}\;\sqrt{4{\pi}_c\;\left(1-{\pi}_c\right)}+{\mathrm{z}}_{\beta}\;\sqrt{2{\pi}_1\;\left(1-{\pi}_1\right)+{\pi}_2\;\left(1-{\pi}_2\right)}}{\pi_1-{\pi}_2}\right]}^2 $$. Because there is only one session of acupuncture treatment and almost no shedding, no loss to follow-up is considered. Thus, the recruitment goal was set at 80 patients.

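### Safety is a stated aim, but the only between-arm inference planned for adverse events is a 5% difference test with 40 per arm, and a non-significant result from it could not support a favourable safety conclusion.

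*Protocol article*

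**What the plan says.** Safety is part of the stated purpose. The Background says the trial "is designed to evaluate the efficacy and safety of acupuncture as an adjunctive treatment to diclofenac for ARCUC", and the Discussion paragraph of the Abstract says: "The finding of this trial will provide evidence on the efficacy and safety of acupuncture for the treatment of ARCUC".

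Under Adverse events, all events are recorded for 7 days and classed as related to treatment or not.

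The Statistical analysis section says of the secondary outcomes that "Student’s *t* test, chi-squared test, Fisher’s exact test or the Wilcoxon rank sum test will be used to test the difference". Adverse events close the list that follows: "credibility and expectancy, and adverse events, between groups according to the distribution of variables". On the threshold it says: "The level of significance will be established at *α* < 0.05 with a two-sided test". It also says: "There is no interim analysis or additional analysis in this trial". Earlier in the section, categorical variables are to be described by frequency and percentage.

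The Sample size section works from the response rate alone, with rates that "are expected to be 70% and 40%, respectively". It concludes: "A sample size of 80 patients (40 in each group) is estimated to have at least 80% power". It gives no expected adverse event rate and no margin for harm.

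**The concern.** A difference test can give evidence of harm. It cannot give evidence that harm is absent unless it had a good chance of detecting the harm in question. Here the test is applied to outcomes that are probably sparse, in a trial sized for a 30-point difference in a common outcome (70% against 40%).

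The article promises evidence on safety but plans no estimate of the adverse event difference with its uncertainty. If needling at the acupoints adds adverse events at a moderate rate, the planned test will often be non-significant. The reader of the trial report then has a p-value and two percentages, and nothing that says how large an excess is still compatible with the data.

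**Working it through.** **Inputs from the article.** 40 patients per arm; two-sided 5%; chi-squared or Fisher's test for categorical outcomes; response 70% against 40%. **Assumed, because the article gives none:** adverse event rates. The sham rate is varied from 0% to 10%, with a 10-point excess under acupuncture. The article does not define 10 points as clinically important; it is used only to show scale.

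**Step 1. The plan's own figure.** With the variance not pooled under the null:

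n per arm = (1.96 + 0.8416)² × (0.7×0.3 + 0.4×0.6) / 0.3² = 7.849 × 0.45 / 0.09 = 39.2, so 40.

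The pooled form gives 42 per arm, and 78.0% power at 40 per arm. The stated 40 per arm is thus reproduced closely enough. It concerns response only and says nothing about harms.

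**Step 2. How often a 10-point excess is missed.** For each pair of rates, sum over all possible counts (a, b) from 0 to 40 the product Bin(a; 40, p₁) × Bin(b; 40, p₀) wherever the test gives p ≥ 0.05.

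| Acupuncture v sham (assumed) | Missed, Fisher | Missed, uncorrected chi-squared |
|---|---|---|
| 10% v 0% | 79% | 42% |
| 12.5% v 2.5% | 81% | 56% |
| 15% v 5% | 82% | 65% |
| 20% v 10% | 84% | 75% |

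The first row can be checked by hand. With no sham events, Fisher's test needs at least 6/40 to reach p < 0.05 (5/40 v 0/40 gives p = 0.055; 6/40 gives p = 0.026). The miss rate is therefore P(a ≤ 5) for Bin(40, 0.10), which is 0.79. Uncorrected chi-squared needs 4/40, and P(a ≤ 3) = 0.42. Against one sham event, Fisher's test needs 8/40.

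**Step 3. Larger excesses.** For 20% v 5% the miss rates are 59% (Fisher) and 43% (chi-squared). For 25% v 5% they are 35% and 24%. A 20-point excess would thus more often be detected than missed at these rates.

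**Step 4. What one plausible result would show.** Take 5/40 against 1/40, a difference of 12.5 - 2.5 = 10 points. Fisher's test gives p = 0.20. The Newcombe interval uses the Wilson limits of each arm: 5.5% to 26.1% for 5/40, and 0.4% to 12.9% for 1/40.

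- Lower limit: 10 - √[(12.5 - 5.5)² + (12.9 - 2.5)²] = -2.5 points
- Upper limit: 10 + √[(26.1 - 12.5)² + (2.5 - 0.4)²] = +23.8 points

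(Limits are computed from unrounded values.) The test would report no significant difference on data compatible with an excess of almost 24 points. Even 0/40 against 0/40 leaves an upper limit of 8.8 points.

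**The case against.** The strongest objection is that the error of inference is not in the document. A reader might infer that the trial will declare acupuncture safe if p > 0.05. No sentence says so; the plan says only that the difference will be tested. That objection stands, and the point is therefore about what the planned test can support, not about a stated decision rule.

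Three further stronger readings also fail:

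- *That adverse events are judged by a test and nothing else.* Events are also classed by relation to treatment, and the general wording on categorical variables promises frequencies and percentages. From patient counts out of 40, a reader could work out an interval. What remains true is that the test is the only between-arm inference planned.
- *That the plan forbids an interval because it excludes additional analysis.* An interval around the same comparison is part of reporting that comparison, so the sentence does not exclude it.
- *That a 10-point excess is missed about 80% of the time, as a property of the trial.* That figure belongs to Fisher's test at assumed low rates. Fisher's test is the natural choice for sparse counts, but the article lists chi-squared too, and its miss rates are lower.

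It may also be said that low power for harms is usual in a trial sized for efficacy, and that interval methods are commonly left to an analysis plan. Both are fair, and neither low power nor the absence of an interval is a fault by itself. But the article does fix a method of inference for adverse events, and that method does not suit the aim it serves. The remedy asks for no more patients.

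**Conclusion.** The point holds in a limited form. Safety is a stated aim, and the only between-arm inference planned for adverse events is a two-sided 5% difference test with 40 per arm. A non-significant result could not support a favourable safety conclusion, although the article does not say it would be used that way.

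The size depends on rates that the article does not give. For assumed sham rates of 0% to 10%, a 10-point excess goes undetected about 79% to 84% of the time with Fisher's test and 42% to 75% with uncorrected chi-squared. It would go too far to say that any important excess will probably be missed: at 25% v 5% both tests detect it more often than not.

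This is a modest improvement to a secondary outcome. The primary analysis is not affected.

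**What to change.** In the Statistical analysis section, take adverse events out of the list of tested outcomes and add text along these lines: for all adverse events, and separately for treatment-related ones, the number of patients with at least one event will be reported per arm, with the risk difference and its 95% confidence interval (for example Newcombe's method). The safety statement will be based on that interval, naming the size of excess that the data do and do not exclude. A p-value above 0.05 will not be taken as evidence of safety.

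The cost is two or three sentences, with no new data and no more patients. The downside is that the safety statement will look less firm than a report of no significant difference.

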## Discussion

ARCUC is one of the worst pains a patient could experience and causes considerable burden for the patients and the society. This trial will evaluate the efficacy of acupuncture in improving the symptoms of ARCUC compared with sham acupuncture.

The effect of NSAIDs has been confirmed by recent meta-analysis [6]. Thus, it is recommended as first-line drugs by international guidelines [1, 20]. However, its application is partly limited for the relatively slow onset time. Previous trial carried out by Lee et al. suggested that acupuncture had a more rapid analgesic onset compared with Avafortan (3.14 ± 2.88 min versus 15.44 ± 7.55 min) [11]. Kaynar’s study also found similar phenomenon in comparing acupuncture with diclofenac [21]. Furthermore, the analgesic effect of diclofenac only last about 7 h based on its half-life elimination of 1.4 h for injection [9]. Interestingly, the persistence of the analgesic effects of acupuncture was found by an individual patient data meta-analysis [22]. Approximately 90% of the benefit of acupuncture would be sustained at 12 months. Combining acupuncture with NSAIDs may be an optional strategy for NSAIDs.

This trial meets the methodological demand for adequate randomization, allocation concealment, and blinding of patients, outcome assessors, and statisticians. Although it is difficult to set a psychologically credible yet physiologically inert control in acupuncture study, superficial insertion at non-acupoints is the most commonly used approach for administering sham treatments [23]. Moreover, all participants will be asked to guess which treatment they have received to test the patient-blinding effects. Blinding patients to interventions is more important, especially when the primary outcome is subjective, such as alleviation of pain. To avoid effects on ARCUC as far as possible, we searched points without effect on ARCUC from both ancient and modern literature. This method of selecting sham points can be seen in Alecrim [24]. There are 16 non-points, but only 2 non-points will be used to each patient in sham acupuncture group. This process of confirming non-points could further eliminate potential effects on ARCUC. After that, the prescription of acupuncture only includes one acupoint, which is very suitable for application in the emergency department due to its simplicity of operator.

This trial has limitations. First, the acupuncturists will not be masked due to the responsibility of providing the intervention. However, the patients and outcome assessors will be blinded to reduce the bias for the subjective symptom. Second, because this study is a single-center trial, the generalization of results to other medical facilities is unknown. At the end of this trial, we hope the results will provide more reliable evidence on acupuncture as an adjunctive therapy for ARCUC.

